### Intermediate outcomes

#### Sanitary survey

In each of the five rounds of the household survey (October 2015; March, July and November 2016; and July 2017), the presence of feces both inside and outside the household compound, and within the *gott* will be observed. The practices of child feces disposal will also be assessed by administering a structured questionnaire and observation.

#### Fly counts

Flies are known to be key vectors transmitting diarrheal pathogens from human feces. We will count the number of flies with glue traps. For all five rounds of the household survey, enumerators will be provided with glue traps of the same length per each household, and they will hang them around the pit-hole of a latrine, if any, before starting the interview. The enumerators will count the number of flies stuck on the glue traps after 30 minutes (Fig. 5).

**Fig. 5 Fig5:**
[figure not shown]
Fly trap

### Data analysis

We will conduct intention-to-treat analysis to assess the effects of improved latrines on child diarrheal reduction. For the main independent variables, the incidence density, 7-day recall period prevalence, and diarrheal duration will be calculated. We will use generalized estimating equations to investigate the effect at the cluster level and a log-binomial model to calculate the incidence rate of diarrhea. Taking into consideration the between-cluster variation by assuming that there are cluster-level effects, we will use the random effects model. We will also conduct a multilevel analysis to explore the effects of coverage of a *gott* on the diarrheal incidence of an individual. (Coverage is defined as low if it is below 33 %; medium, 33–66 %; and high, above 66 %).

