#### Incidence density of diarrhea in terms of child-weeks

The expected value of the incidence density, E (*s*^2^), is given by$$ \mathrm{E}\left({\mathrm{s}}^2\right) = \lambda \mathrm{A}\mathrm{v}\left(1/{\mathrm{y}}_{\mathrm{j}}\right) + {\sigma^2}_{\mathrm{c}}=\lambda \mathrm{A}\mathrm{v}\left(1/{\mathrm{y}}_{\mathrm{j}}\right) + {\mathrm{k}}^2{\lambda}^2, $$

where λ is the true mean rate, *y*_*j*_ corresponds to the child-weeks of follow-up in the *j*^th^ cluster, Av() indicates the mean overall clusters, *σ*_*c*_^2^ is the between-cluster variance of the true rates, and *k* is the coefficient of variation of those rates [17]. Based on the preliminary survey, the overall diarrheal rate in the 48 *gotts* was 0.18 (or 18 cases per 100 child-weeks). The empirical standard deviation of the observed diarrhea rates was 0.092189, and the average of the reciprocal child-weeks per neighborhood was 0.001667. Therefore, *k* was estimated as$$ \begin{array}{c}\hfill {\sigma}^2={0.092189}^2-0.18\times 0.001667=0.008199,\hfill \\ {}\hfill \hfill \\ {}\hfill \mathrm{and}\;\mathrm{therefore},\;k=\surd \left(0.008199/0.18\right)=0.213422.\hfill \end{array} $$

We assumed that the diarrhea rate in the control *gotts* remained constant at λ_0_ = 0.18, and we required 90 % power (*z*_*β*_ = 1.28) if the intervention reduced the diarrhea rate by 21 %. Assuming 600 child-weeks of observation (24 weeks of follow-up for 25 children) in each *gott*, the number of neighborhoods required for each treatment group is given by c = 1 + (1.96 + 0.28)^2^[(0.18 + 0.1422)/600 + 0. 213422^2^(0. 18^2^ + 0. 1422^2^)]/(0.18 − 0.1422)^2^ = 22.55.

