### Health outcome assessment with a sanitation calendar

We distributed a sanitation calendar to all registered households beginning in December 2015 and asked mothers or caregivers to mark “O” or “X” depending on the presence of diarrheal disease of her youngest child every day over the 12-month period of longitudinal observation from December 2015 to November 2016. WaSH promoters have been monitoring the recording status of the sanitation calendar on a weekly basis and continue to educate and encourage mothers or caregivers to continue recording appropriately.

We devised an incentive mechanism to encourage the mothers or caregivers to record diarrheal episodes on the sanitation calendar properly by establishing a system where a well-maintained calendar can be used as a voucher. A well-recorded calendar, regardless of whether it contains Os or Xs will be exchanged with a gift-in-kind, probably sanitation-related materials such as soaps, nail clippers, toothpastes, or the like. WaSH promoters will take a photo of the sanitation calendar using a mobile phone and submit to a supervisor and the team leader. For the study, diarrhea is defined as three or more watery stools in 24 hours according to the WHO definition.

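### The model named for the diarrhea incidence rate (log-binomial) estimates a ratio of proportions, not the rate ratio per child-week that the trial was sized on; how far the two differ depends on a binary unit the protocol does not name

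*Protocol article*

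**What the plan says.** The Data analysis section of the protocol article names three diarrhea measures as separate quantities: "the incidence density, 7-day recall period prevalence, and diarrheal duration will be calculated". It then assigns "a log-binomial model to calculate the incidence rate of diarrhea". It also mentions generalized estimating equations, a random effects model and a multilevel analysis, but attaches no count or rate distribution to any of them.

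The incidence outcome has its own sample size section, headed "Incidence density of diarrhea in terms of child-weeks". The overall rate there "was 0.18 (or 18 cases per 100 child-weeks"). The variance is a Poisson term for child-weeks of follow-up plus a between-cluster term. The target is stated as "we required 90 % power" "if the intervention reduced the diarrhea rate by 21" percent, with 24 weeks of follow-up for 25 children in each gott.

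The Primary endpoint section says that the caregiver records the youngest child's episodes each day. The sanitation calendar section has this continue "over the 12-month period of longitudinal observation from December 2015 to November 2016", with a daily mark for diarrhea present or absent.

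**The concern.** An incidence density counts new episodes, including repeat episodes in the same child, and divides by time observed. A log-binomial model describes the probability that a yes/no outcome is yes, and its exponentiated coefficient is a risk or prevalence ratio. The two agree only when the event is rare within the chosen unit and each event occupies one unit.

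The article pairs this model with a rate that it has already defined, powered and listed apart from prevalence. An analyst who follows the text must first turn the calendar into yes/no records, by child, by week or by day, and nothing in the article fixes which. The choice moves the expected ratio from about 0.79 to almost 1, and it could be made after the data are seen.

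**Working it through.** **Inputs from the sample size section.** Control rate λ0 = 0.18 per child-week; λ1 = 0.18 × (1 − 0.21) = 0.1422; y = 600 child-weeks per gott; k = 0.213422 as printed; z values 1.96 and 1.28. Calendar duration is 12 months, taken as 52 weeks.

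**The plan's own figure.** c = 1 + (1.96 + 1.28)² × [(0.18 + 0.1422)/600 + 0.213422² × (0.18² + 0.1422²)] / (0.18 − 0.1422)²
= 1 + 10.4976 × [0.000537 + 0.002397] / 0.001429 = 22.55 gotts per arm.
This matches the article. The printed expression shows 0.28 in place of 1.28, which would give 11.30, so that is a typographical slip. The calculation is for a rate difference, and the rate ratio behind it is 0.1422/0.18 = 0.79. The value of k does not enter anything below.

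**Unit = child, ever/never (assumed).** Expected episodes per child are 0.18 × 24 = 4.32 and 0.1422 × 24 = 3.41; over 52 weeks they are 9.36 and 7.39. With Poisson episodes the risk over w weeks is 1 − exp(−λw).

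| Weeks | Control risk | Intervention risk | Risk ratio | Share of the 21 % reduction kept |
|---|---|---|---|---|
| 24 | 0.9867 | 0.9671 | 0.980 | about 9 % |
| 52 | 0.99991 | 0.99939 | 0.9995 | about 0.3 % |

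A log-time offset cannot rescue the child-level model: a mean proportional to time would have to reach 4.32 at 24 weeks, and a probability cannot exceed 1.

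**Sensitivity to differences between children.** With gamma frailty of variance v (assumed), the risk is 1 − (1 + vλw)^(−1/v).

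| v | Ratio, 24 weeks | Ratio, 52 weeks |
|---|---|---|
| 0.5 | 0.960 | 0.985 |
| 1 | 0.952 | 0.975 |
| 2 | 0.948 | 0.966 |

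At 24 weeks, 19 to 25 % of the planned reduction is kept.

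**Power for ever/never.** With 600 children per arm, Poisson episodes and clustering ignored, power is 62 % at 24 weeks and 7 % at 52 weeks. Dividing n by the prevalence design effect of 2.14 (an assumption for this outcome) gives 34 % and 5 %. The plan asks for 90 %.

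**Unit = child-week.** (1 − exp(−0.1422))/(1 − exp(−0.18)) = 0.1326/0.1647 = 0.805, which keeps about 93 % of the reduction. With frailty variance 0.5 to 2 the ratio is 0.811 to 0.825.

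**Unit = child-day.** (1 − exp(−0.1422/7))/(1 − exp(−0.18/7)) = 0.792.

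The week and day figures count each episode once, in the unit where it starts. The calendar, however, marks every day with diarrhea. The proportion of marked days is approximately episode rate × mean duration, so its ratio is 0.79 × (ratio of mean durations). It equals the rate ratio only if duration is the same in both arms, and the trial sets out to study duration as an outcome in its own right. By week, two episodes in one week count once and one episode spanning two weeks counts twice.

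**The case against.** The strongest reply is that no section proposes collapsing a child to ever/never. The sample size is in child-weeks, the calendar is marked daily and it is checked weekly, so the natural yes/no record is the week or the day. On those units the ratio is 0.81 or 0.79, close to target. This stands. A reader might infer from the child-level figures that the plan will hide nearly all of the effect; the article does not support that, because it never names the child as the unit.

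A reader might also infer that children with incomplete calendars would be treated as fully observed. That too follows only from ever/never. A binomial model for weeks with diarrhea out of weeks recorded carries observed time in its denominator.

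It is also fair that the sample size section does not say whether a case is an episode or a week with diarrhea. On the second reading, a child-week log-binomial model returns 0.1422/0.18 = 0.79 exactly. But it would then estimate a weekly prevalence, whereas the analysis section lists incidence density apart from 7-day prevalence and the calendar is described as recording episodes.

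Finally, the record unit and the handling of repeat episodes are details that an article may leave to a fuller plan, and clustering is already provided for through the other models named. That answers a complaint about missing detail. It does not answer the stated pairing of a binomial model with an incidence rate.

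**Conclusion.** The model is wrong as written for the outcome it is assigned to. The rate ratio of 0.79 per child-week that the trial was sized on is not what a log-binomial model estimates, whichever binary unit is chosen.

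The numerical consequence is conditional. Under an assumed ever/never outcome per child, the ratio is about 0.98 at 24 weeks and 0.9995 at 52 weeks with Poisson episodes, or 0.95 to 0.96 at 24 weeks with assumed frailty variance 0.5 to 2; most of the effect is lost. With week or day records the numerical loss is small, and the fault is one of meaning: the estimate is a proportion of time units with diarrhea and blends incidence with duration.

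Confidence is high on the mismatch and low on which unit would be used. The matter concerns a non-primary outcome. The primary endpoint is 7-day prevalence, for which a log-binomial model is suitable. It should be corrected, but it does not threaten the primary conclusion.

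**What to change.** In the Data analysis section, replace the log-binomial statement for incidence with this: calendar episode counts per child will be analysed with a Poisson or negative binomial model, by GEE or with random effects, allowing for clustering by gott, with the log of child-weeks of valid calendar recording as offset, and the incidence rate ratio will be reported. Keep the log-binomial model for 7-day prevalence.

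The cost is one sentence and standard software. Design and data collection do not change, since the daily calendar already supplies the counts and the observed time. Counting episodes needs a stated rule for when a new one begins; if a fuller plan already contains that rule, a cross-reference is enough. The change should be made before the calendar data are analysed by arm.

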## Discussion

This study seeks to assess the effects of improved sanitation on the health gains of children under 5 years of age and to explore the behavioral factors associated with latrine improvement. Several studies [13–15] have been conducted for a similar purpose with rigorous methodology in South Asian countries; however, those studies failed to reach universal or sufficient coverage of improved latrines. Furthermore, the results of recent randomized controlled trials cannot represent the effect of Community-Led Total Sanitation because they provided material or financial subsidies, although these were limited to the marginalized groups in the community. For example, a recent study [20] on improved sanitation, conducted in Bangladesh, revealed that subsidies could increase latrine ownership both in subsidized and unsubsidized households; however, those authors did not investigate the effects of the approaches for latrine improvement on scalability and sustainability, nor did they explore the effects on maintenance. For this study, we strictly applied the main principle of Community-Led Total Sanitation, paying close attention to the potential for scalability and sustainability. In the trial, community members will fully contribute to constructing their own household latrines, including digging a pit-hole; obtaining materials for the slab, pit-hole cover, walls, and roof; and completing installation.

For the study, a sanitation calendar has been devised to track child diarrhea more efficiently. We estimate the incidence density of diarrhea. With the sanitation calendar, the potential of recall bias [21] and respondent fatigue [22] due to frequent visits, which were the limitations of previous studies, are expected be reduced. Moreover, the sanitation calendar will help us to investigate the effects of improved sanitation on the duration of diarrheal diseases through the daily recording of diarrheal episodes. Assessing the effects of improved sanitation on the diarrheal duration has continuously been recommended as a future study topic in previous studies.

To ensure objectivity and avoid information bias, latrine improvement status will be photographed with tablet PCs or mobile phones provided to enumerators and WaSH promoters. Assessments of the latrine improvement status will be made by supervisors and team leaders, not by the enumerators or WaSH promoters, which helps avoid overestimating the coverage of improved latrines. Latrine improvement status will be scored on the basis of the photos taken. Using the scored results, the degree of the effects of the improved latrines will be explored according to the improved status.

To avoid contamination between the intervention and control *gotts* in the same *kebelle*, we excluded any neighboring *gotts* of either intervention or control *gotts* from selection, thus making those *gotts* serve as a buffer zone [23]. In this trial, keeping records on the sanitation calendar is one of the most important features. In order to encourage mothers or caregivers to record diarrheal incidence every day, WaSH promoters will visit registered households on a weekly basis. The sanitation calendar will be photographed on this visit, and the supervisors and team leader will randomly revisit some of the households to verify the results. The system of encouragement and verification will be strictly maintained, particularly during the first 2 months of the intervention period, so the mothers or caregivers of registered households will be familiar with recording cases of diarrhea. A community meeting will be convened every month, and the WaSH promoter will correct substantial errors related to sanitation calendar utilization.

Our intervention is not to provide any financial nor material subsidy to community members. Rather, our intervention is to encourage community members to construct latrines for their own household members using locally available materials. We strictly comply with the key principles of Community-Led Total Sanitation (CLTS). Therefore, like all the previous studies, we have similar limitations such as the possibility of insufficient coverage.

This study will provide sound evidence for determining the effects of improved latrines on the prevalence, incidence density, and duration of diarrheal disease of children under five.

### Trial status

Trial recruitment had not commenced as of October 23, 2015.

## Abbreviations

CLTSH: Community-Led Total Sanitation and Hygiene
MDGs: Millennium Development Goals
NRERC: National Research Ethics Review Committee
SNNPR: Southern Nations, Nationalities, and Peoples’ Region
WaSH: Water, Sanitation, and Hygiene.
